#### Pre-visit coaching

After participants in the intervention group have completed their last session, the RA will meet with the patient prior to their next office visit with their HIV provider. This one-time individual coaching session is designed to reinforce application of skills learned during the group training. A separate manual and fidelity checklist has been developed for this one-on-one session. Key tasks for the session are summarized below (Table 3).

**Table 3 Tab3:** Key tasks for pre-visit coaching

•Bring iPod/ePHR (reminding the patients to bring their iPod to their patient coaching session and to their subsequent doctor visit).
•Preparation of questions (ensuring that the patient has identified and recorded in their iPod key questions to ask their clinician).
•Application and rehearsal of skills (coaching the patient through role play asking his/her questions.

#### Clinician training

We will train clinicians to engage patients in the intervention group, (i.e. those who present with their ePHR in the visits) through an educational “lunch and learn” session that is CME-accredited. These educational sessions will address the purpose of the project and basic clinician behaviors to facilitate empowerment. Drs. [name] and [name] will lead these sessions. We will use training approaches used in previous studies [17–19] that are supported by systematic reviews of randomized controlled trials of clinician training [20, 21]. We include explicit demonstrations using brief videos [22]. We will show examples of effective and ineffective communication. These include encouraging the patient to use their ePHR for questions, praising patients for engagement, helping patients prioritize their questions, and providing patients with relevant information to enter into their ePHR. Clinicians will be encouraged to download URHealth onto their own personal devices, in order to familiarize themselves with the ePHR and to enable them to provide ongoing support and effective answers to questions from their patients about use of the ePHR.

### Training manual

We have developed a detailed training manual for instruction of project staff and peers as facilitators to conduct the patient group sessions. The onsite train-the-trainers sessions will focus on competency in conducting each of the six group sessions with specific attention to displaying enthusiasm, active engagement of group through questions and sharing, staying on task and time, and ensuring all members are able to rehearse particular skill during the session. We will assess fidelity using an observation checklist applied to intervention group videotapes. All train-the-trainer sessions will be recorded to train new staff as well as provide refresher training if drift occurs. After study completion, these trainings will be posted online to enhance dissemination and sustainability.

### Usual care

Participants assigned to this group will receive usual care from their HIV clinician during the duration of the study. They will receive the same surveys at the same time periods, T01–T3 as those assigned to the intervention group. Following the completion of their final assessment (T3), participants in the usual care group will receive the iPod loaded with the URHealth application, and will be provided with the training manual to assist with self-teaching on the use of the application.

### Study outcomes and measures

Our study measures reflect our patients’ choice of outcomes related to empowerment including activation, eHealth literacy, and greater decision-making and involvement in care. These outcomes will be assessed using validated scales with sound psychometric properties and through chart abstraction data. These are summarized below (Table 4).

**Table 4 Tab4:** Study measures, data source, and timing

Construct (Hypothesis)	Measure	Data type source	Collection points
Participant characteristics			
Demographics	Standardized questions	Survey	T0
Computer experience	Standardized questions	Survey	T0
Health history	Standardized questions	Survey	T0
Aim 1 (Empowerment)			
Patient activation (H1.1)	PAM [56, 57]	Scale	T0, T1, T2
Decision making (H1.1)	Decision Self Efficacy Scale [26]	Scale	T0, T1, T2
eHealth Literacy (H1.1)	eHEALS [23, 24]	Scale	T0, T1, T2
Involvement in Care (H1.2)	Perceived Involvement in Care [25]	Scale	T0, T1, T2
Aim 2 (Evidence-based care)			
HIV adherence self-efficacy (H2.1)	ASES [29]	Survey	T0, T1, T2
Adherence to cART (H2.1)	Past week adherence [28]	Survey	T0, T1, T2
HIV viral load <50 (H2.2)	HIV viral loads (both actual level; and whether undetectable or not)	Chart abstraction	T0, T2
Evidenced based preventive care	Cancer screening/immunizations [58]	Chart abstraction	T0, T3
Aim 3 (Health)			
Physical and Mental health/Quality of Life (H3.1)	SF-12 [27]	Scale	T0, T1, T2
Aim 4 (Moderators)			
Low Activation (H4.1)	PAM and eHEALS (<median)	Scales	T0
Minority race/ethnicity (H4.2)	Standardized questions	Survey	T0
Low education (4.2)	Standardized questions	Survey	T0
Clinician patient centeredness	Instrument on Doctor-Patient Communication Skills. [30]	Scale	

#### Patient empowerment

Our primary outcome is patient empowerment assessed using the Patient Activation Measure (PAM). We will capture related additional dimensions of empowerment including eHealth literacy (eHealth Literacy Scale eHEALS [23, 24]), patient involvement in their care (Patient Involvement in Care [25]) and, patient confidence in their health care decision making (Decision Making Self Efficacy Scale [26]).

#### Patient health status

We assess patient’s mental, social and overall health based on the well-validated Medical Outcomes Study SF–12 [27]. It provides an overall score and relevant subdomain scores.

#### Adherence measures

We will assess adherence and receipt of evidence-based care using a series of adherence related measures and data abstracted from the EHR. These include validated measures of adherence to cART [28] and patient self-efficacy related to adherence, [29] in addition to viral load values (from medical records) and a summary index of evidenced-based care (from medical records). The index will be derived based on receipt of the number of evidence-based measures received divided by the total number the patient is eligible for. These include those receiving an A or B rating by the US Preventive Services Task Force, e.g. breast, cervical and colorectal cancer screening, immunizations, lipid screening,

#### Patient social disadvantages

We will assess race (White, Black, Asian, Other) and ethnicity (Latino or not), age, and sex based on self-report. We define low education as absence of any high school degree. Low activation and low eHealth literacy will be based on less than the median value on the PAM and eHEALS.

#### Clinician communication

We will assess the communication skills of clinicians using the Doctor-Patient Communication Skills instrument [30]. This validated scale assesses key aspects of clinician communication from the perspective of the patient. We will minimize patient reporting bias by aggregating clinician scores across patients. We chose to use patient ratings of clinicians rather than observer ratings because these are more patient-centered measures and patients’ perceptions probably have the greatest impact on patients’ behavior; as well as their lower costs and greater capacity for pragmatic implementation. We chose this scale over other patient reported measures of clinician communication because it comes closest to measuring the clinician competencies that we address in our clinician training and which our patients tell us are most meaningful to them.

### Preliminary data

We piloted the intervention with 32 PLWH.

We obtained pre and post assessments on the participants and assessed change scores. Our pilot data below (Table 5) show improvement in key measures. In addition, participants with the least education, activation, and least eHealth literacy benefited the most. Specifically, those with less than a high school education and those with lower activation or lower eHealth literacy (i.e. below the median for the group) showed larger improvements in adherence, eHealth literacy, perceived involvement in care, decision in self-efficacy, and patient activation than those with higher levels.

**Table 5 Tab5:** Characteristics of PLWH in pilot study (*n* = 32)

Age mean (Standard deviation)	49 (10.2)
Gender^a^	
Female	16 (50 %)
Male	15 (47 %)
Race/ethnicity	
Hispanic	8 (25 %)
Non-Hispanic White	1 (3 %)
Non-Hispanic Black	20 (63 %)
Other	3 (6 %)
Computer Use (% none)	7 (22 %)
Insurance Type	
Public (Medicaid/Medicare)	30 (94 %)
Private	0 (0 %)
ADAP	4 (6 %)
Education	
<High school	10 (31 %)
High school diploma or GED	6 (19 %)
More than high school	16 (50 %)
Annual Income^a^	
<$20,000	29 (91 %)
$20,000–29,999	2 (6 %)
≥$30,000	0 (0 %)

^a^Note not all categories total 100 % due to missing values

### Planned analysis

Following collection and cleaning of data (T0–T3), the underlying assumptions of all analyses will be checked using appropriate graphical and numerical methods [31]. Data accuracy will be investigated upon discovery of any outliers or influential data points. If an outlier is detected, we will truncate the outlier by assigning a reasonable value or replacing it using the adjacent values from the remaining data. We will try to utilize all data points in the final analysis.

The proposed study adopts a randomized repeated measures pre-test/post-test design and our analytic plan reflects this design. We will use generalized estimating equations (GEE) to obtain robust estimates and to account for the repeated measures study design and the correlated data structure of subjects nested within study site [32]. The chosen link function for the models will be appropriate for the distribution of each outcome. Unless otherwise stated, all statistical tests will be performed at the two-tailed 5 % level of significance. Likewise, 95 % confidence intervals will be constructed for estimation of effects (e.g., difference in outcomes between intervention and control groups). We will use Dunnett and Hsu’s methods to control for multiple comparisons in secondary outcomes [33]. All analyses will be performed with SAS® statistical software version 9.3 (SAS Institute, Cary NC).

We will summarize frequencies of categorical variables and means or medians for continuous and ordinal variables. Continuous variables with skewed distributions will be transformed to approximate normality. We will construct tables that display baseline characteristics for participants, overall and by (blinded) group assignment. We will compare baseline information on participants including demographic characteristics, previous computer use, and health factors. We will assess whether attrition differs across baseline characteristics or by group assignment and adjust for differences if present using multiple imputation if necessary. We will conduct intention-to-treat analyses.

Every effort will be made to facilitate and encourage participants’ completion of all surveys. In the event that missing data occur, we will attempt to contact participants and obtain the data or to find out why the surveys or items are missing. The reasons for missing data will be documented and the mechanism for missing data will be examined [34]. If needed, data will be imputed and a weighted generalized estimating equations (WGEE) model will be applied using the inverse probability of missingness as the sample weight [35]. Sensitivity analyses will be performed to determine the impact of key assumptions.

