### Data management and quality control

An RA will enter data into a laptop computer and upload it into the Web-based RedCap database [16]. Invalid responses and outliers (those falling outside of response ranges) will be corrected immediately. Quality reports will be conducted weekly using RedCap analytic tools to assess missing data and rates of invalid responses. All laptops will be fully encrypted and password protected. Files linking participant names with study ID numbers will be stored separately on a secure, password protected server.

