### Aim 2: Increase PLWH’s receipt of evidence-based care

To assess H 2.1 (improvement in patient improve patient confidence in adhering to combination antiretroviral treatment (cART), self-reported adherence to cART, and HIV viral suppression), we will substitute these dependent variables in the above models. Similarly for H 2.2 (improvement in evidence-based care), we will index for evidence-based care for the dependent variable. This index will be created by passed on ratio of interventions that the patient received versus the number they were eligible for.

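### The outlier rule overwrites detected outliers without requiring that they be shown to be errors, so genuine outcome values, viral-load levels most of all, can be altered at the analyst's discretion

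*Protocol article*

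**What the plan says.** Two parts of the protocol article deal with extreme values.

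- **At data entry** (Data management and quality control): "Invalid responses and outliers (those falling outside of response ranges) will be corrected immediately".
- **At analysis** (Planned analysis): "Following collection and cleaning of data (T0–T3), the underlying assumptions of all analyses will be checked". Then: "Data accuracy will be investigated upon discovery of any outliers or influential data points". The next sentence gives the action for a detected outlier: "we will truncate the outlier by assigning a reasonable value or replacing it using the adjacent values from the remaining data".

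The same section already has tools that leave every observation as recorded: "Continuous variables with skewed distributions will be transformed to approximate normality", link functions suited to each outcome, and robust GEE estimates. It also states an aim to use all data points.

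Table 4 lists viral load, taken from charts at T0 and T2, as "HIV viral loads (both actual level; and whether undetectable or not", with a threshold of 50. The Aim 2 analysis makes viral suppression a dependent variable for H 2.1. The primary outcome is the Patient Activation Measure (PAM).

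**The concern.** The overwrite sentence sets no condition that the value be wrong. A laboratory result confirmed in the chart is treated in the same way as a keying error. Since entry checks have already dealt with impossible responses on the survey scales, what remains to be overwritten is mostly legitimate data.

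Three things are at stake. First, means and arm differences can shift because real extremes are pulled in. Second, edited values enter the model as if observed, so the variance is understated and intervals become too narrow. Third, although the rule is written in advance, which values count as outliers and what replaces them are chosen once T0–T3 data are in hand. Viral load is the outcome where this matters most, because its outlying values are the failures that Aim 2 sets out to reduce.

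**Working it through.** **Plan's own figures.** The article gives no figure for the outlier rule. Its sample size is 360 enrolled with 15% drop-out: 360 × 0.85 = 306 analysed, or 153 per arm if allocation is 1:1 (assumption). The stated detectable effect of 0.51 reproduces with 8 sites, ICC 0.0207 and t quantiles on 6 df: design effect 1 + (306/8 − 1) × 0.0207 = 1.771, and (t₀.₉₇₅ + t₀.₈₀) × √(4/306 × 1.771) = 0.510. It plays no part in what follows.

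**Step 1: what the rule acts on.** Setting the two sections side by side, out-of-range responses go at entry and the overwrite comes after cleaning. For bounded scales that leaves in-range scores. Chart viral loads have no response range, so both genuine high values and abstraction errors reach the rule, and it does not separate them.

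**Step 2: why viral load can be hit hard.** Take the usual box-plot fence, Q3 + 1.5 × (Q3 − Q1), as one possible flagging rule (assumption). Suppose 85% are suppressed and coded 20 copies (assumption). Then Q1 = Q3 = 20, the fence is 20 + 1.5 × 0 = 20, and all 306 × 0.15 ≈ 46 detectable values are flagged. The nearest unflagged value is 20, which is below 50.

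**Step 3: how far this depends on the choices.** Simulation with 153 per arm and 1,000 replicates. Suppressed = 20 copies; failures lognormal (log10 mean 3.8, SD 0.9, floor 50). Flagged values are replaced by the largest unflagged value, and the below-50 status is re-derived from the edited level. Power is for a simple two-proportion test. All of this is assumed.

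| Suppressed, control/intervention | Failures flagged: fence raw / log10 | Failures flagged: 3 SD raw / log10 | Recorded failures after fence, control vs intervention (raw; log10) | Power before → after fence (raw; log10) |
|---|---|---|---|---|
| 50/60% | 38% / 0% | 3% / 0.1% | 50 vs 40%; 50 vs 40% | 0.41→0.41; 0.45→0.45 |
| 60/75% | 63% / 4% | 4% / 1% | 40 vs 25%; 40 vs 25% | 0.79→0.79; 0.81→0.80 |
| 70/80% | 93% / 72% | 5% / 4% | 16 vs 11%; 16 vs 11% | 0.54→0.27; 0.53→0.29 |
| 75/85% | 99.9% / 99% | 6% / 9% | 0.3 vs 0.2%; 0.6 vs 0.4% | 0.59→0.01; 0.59→0.01 |
| 80/90% | 100% / 100% | 8% / 21% | 0 vs 0%; 0 vs 0% | 0.71→0.00; 0.68→0.00 |

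Under the 3 SD rule the suppression power was the same before and after in every row: levels were altered, status was not. At 75/85% the expected failures are 153 × 0.25 + 153 × 0.15 = 61.2. The raw fence flags 0.999 × 61.2 ≈ 61 of them; the raw 3 SD rule flags 0.062 × 61.2 ≈ 4.

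A second distribution (detectable values log-uniform from 10² to 10⁵, N = 306, raw-scale fence) flags about 0.70–0.72 of detectable values at 70% undetectable, 0.91–1.00 at 75%, and 1.00 at 80–85%. On the log10 scale at 70% the share is about 0–0.44, depending on the code used for undetectable.

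**Step 4: the primary outcome.** On a 0–100 scale with mean 60 and SD 15 (assumed), the fence flags 0.66% of values and the 3 SD rule 0.14%. That is 306 × 0.0066 ≈ 2.0 and 306 × 0.0014 ≈ 0.4 values per assessment.

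**The case against.** The strongest reply is that the damaging scenario uses a fence the article never names. Planned analysis speaks only of graphical and numerical checks, and under a 3 SD rule the suppression result does not move. That stands, and it limits the size of the point.

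Suppression is also listed as its own yes/no outcome, and a binary variable has no outliers in this sense. A reader might infer that the plan turns viral failures into successes. The article does not say so: that would need levels to be edited first and status re-derived from them, and no section states this order. Nor does any section exclude it.

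A reader might also infer that the primary analysis or H 4.1 is seriously distorted because low PAM scorers are pulled in. This is not supported either. Few values on a bounded scale would be flagged, and H 4.1 defines low activation as below the median, so a very low score moved to a neighbouring value stays in the low group.

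One could read outlier at the analysis stage in the data-entry sense, as a value beyond the response range. The analysis section pairs the word with influential points and model checks, which points to a wider meaning. Even on the narrow reading, an error that cannot be resolved should be missing, not given an invented value.

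The accuracy check, transformation, link functions, robust GEE and general sensitivity analyses all help. But replacement does not depend on the check, and the sensitivity analyses are not tied to this rule. Finally, threshold, replacement value and blinding may be fixed in an analysis plan not shown, so their absence is not held against the article. What remains is the unconditional instruction itself.

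**Conclusion.** The point holds as a fault in a stated rule. Followed as written, it changes genuine values without proof of error, leaves room for discretion after the data are seen, and understates variance. It does so where value-preserving remedies are already planned.

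The viral-load level is the most exposed outcome. The below-50 result is affected only if status is derived from edited levels, flagging is fence-like and suppression is high. Under those assumptions the effect runs from negligible (at or below about 60/75% suppressed) through a halving of power (70/80%) to near-complete loss of recorded failures (75/85% and above). The effect on the primary PAM comparison is small. The article gives neither suppression rates nor a flagging rule, so no single figure can be attached to this trial.

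**What to change.** Replace the overwrite sentence with wording to this effect:

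- Outliers are queried against source.
- Values confirmed at source are kept unchanged in the primary analysis.
- Values shown to be errors that cannot be recovered are set to missing and handled under the missing-data plan.
- Viral suppression is derived from unaltered viral loads.
- Any truncation or winsorising is confined to a sensitivity analysis, with a threshold fixed in advance (for example the 1st and 99th percentiles) and applied blind to arm.

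Skewed viral-load levels can be handled with the transformation and robust GEE already planned. The cost is a change of wording and one extra sensitivity run. No design or data-collection change is needed.

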**Methods/Design:**

Randomized controlled trial of a multimodal intervention designed to activate persons living with HIV. The intervention includes four components: 1) use of a web-enabled hand-held device (Apple iPod Touch) loaded with a Personal Health Record (ePHR) customized for HIV patients; 2) six 90-minute group-based training sessions in use of the device, internet and the ePHR; 3) a pre-visit coaching session; and 4) clinician education regarding how they can support activated patients. Outcome measures include pre- post changes in patient activation measure score (primary outcome), eHealth literacy, patient involvement in decision-making and care, medication adherence, preventive care, and HIV Viral Load.

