## Methods

### Study design

We will conduct a parallel randomized controlled trial. This design allows us to examine pre- and post-assessments of participants randomized to the intervention (treatment group) compared to participants randomized to usual care (control group). Given our focus on individual patients, the nature of our intervention, including its reliance on training and specific tools, the risk for contamination between participants will be relatively small. Any such contamination will bias results towards the null. We considered other designs including randomizing by practice site (cluster RCT), stepped wedge and staggered enrollment trials, but did not choose these designs due to few clusters, data collection burden, and relatively short funding time frame (3 years).

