### Procedures for randomization and allocation

Sequential identification (ID) numbers will be generated by our study biostatistician using computer generated random numbers stratified by site (Rochester or NYC) to minimize potential site variation between groups. Assignments will be concealed in sealed opaque, envelopes that contain the group assignment. Following confirmation of the participant’s eligibility, informed consent, and completion of the baseline assessment (T0), the RA will open the envelope and notify the participant whether they have been assigned to the intervention or usual care group.

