### Aim 1: Improve PLWH’s empowerment

To assess H 1.1 (Improvement in patient activation; decision making ability; and perceived knowledge, comfort, and perceived skills at finding, evaluating, and applying electronic health information to health problems), we will compare changes in patient activation (primary outcome), eHealth literacy, and decisional self-efficacy outcomes by assigned randomization group using GEE models that control for baseline scores. All models will be adjusted for any potential confounders identified by the initial analyses. We will use the same approach to assess H 1.2 (substituting Perceived Involvement in Care).

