### Power

The number of participants included in the intervention group and the usual care groups is based upon a series of power analyses. For H 1.1 – H 3.1, we estimated detectable difference using the method described by Donner and Klar, [36] using 8 study sites total, a significance level of 0.05, and a minimum power of 80 %. The intra-cluster correlation (ICC = 0.0207) was estimated from our pilot data and is consistent with other studies [37]. We plan to enroll 360 participants to allow for attrition and assume a 15 % drop-out rate. Thus, we will be able to detect an effect size of 0.51 for each of the measures in Table 6. For H 4.1 and H 4.2, we ran Monte Carlo simulations to determine that we will have a minimum of 80 % power for the interactions [38].

**Table 6 Tab6:** Change in empowerment dimensions (effect size) by participant education, activation or eHealth literacy

Empowerment dimension	<High school	High school	>High school	Low activation	High activation	Low eHealth literacy	High eHealth literacy
HIV adherence self-efficacy	0.15	−0.64	−0.19	0.18	−0.38	−0.02	−0.05
eHealth literacy	0.85	0.35	0.61	0.98	0.18	0.94	0.35
Perceived Involvement in Care	0.57	0.37	0.24	0.61	0.11	0.48	0.26
Decision self-efficacy	0.81	0.23	0.34	0.86	0.16	0.48	0.52
Patient Activation	0.50	−0.85	0.24	0.52	−0.155	0.32	0.11

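### The primary GEE does not name its cluster unit: 8 site clusters need a small-sample correction, participant clusters leave one-arm training groups unmodelled, and covariates are chosen from the data

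*Protocol article*

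**What the plan says.** All references are to the protocol article.

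- **Planned analysis**: the GEE is chosen for robustness and, as its second stated purpose, "to account for the repeated measures study design and the correlated data structure of subjects nested within study site". Tests: "all statistical tests will be performed at the two-tailed 5 % level of significance". The section names no cluster unit, reference distribution or small-sample correction.
- **Aim 1** (analysis): the primary comparison of PAM change controls for the baseline score. Then: "All models will be adjusted for any potential confounders identified by the initial analyses".
- **Procedures for randomization and allocation**: participants are randomised individually, using "computer generated random numbers stratified by site (Rochester or NYC"), so the stratum has two levels.
- **Study design**: a site-randomised trial and other designs were considered, but the authors "did not choose these designs due to few clusters, data collection burden" and a short funding period.
- **Abstract, Methods/Design**: the intervention includes "six 90-minute group-based training sessions in use of the device, internet and the ePHR". Usual care has no such groups.
- **Power**: the detectable difference was found "using 8 study sites total, a significance level of 0.05, and a minimum power of 80" %, with a site ICC of 0.0207, 360 enrolled and 15% drop-out.

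**The concern.** A standard GEE has one level of independent cluster. For a single GEE to cover both repeated measures and correlation within site, that cluster would have to be the site, which leaves 8 clusters. Sandwich standard errors are too small with so few clusters unless corrected. If the cluster is instead the participant, the repeated measures are covered but everyone is treated as independent of everyone else. The intervention arm is trained in groups, and the Group training section presents shared learning as central to how the intervention works. Some correlation within groups, in one arm only, is therefore plausible by the trial's own rationale.

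What is at stake is the p-value and confidence interval for the primary outcome. A second, separate issue is that the covariate set of the primary model is left to be decided from the data.

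**Working it through.** **Inputs from the article.** 8 sites (4 Rochester, 4 New York area); ICC 0.0207; 360 enrolled; 15% drop-out; two-sided 5%; two follow-up surveys (T1, T2); baseline score as covariate.

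**Assumed, because the article does not give them.** Site sizes (equal; 23-55; 8-80); 1:1 allocation within region; training groups of 6-10; group ICC 0.0207, 0.05 or 0.10. The simulations also need within-person correlations.

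**1. The plan's own figure.** Evaluable: 360 × 0.85 = 306, or 153 per arm and 306/8 = 38.25 per site. Design effect: 1 + (38.25 − 1) × 0.0207 = 1.771. As if sites were randomised, 4 per arm:

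d = (t₀.₉₇₅,₆ + t₀.₈₀,₆) × √(2 × 1.771/153) = (2.447 + 0.906) × 0.1522 = 0.510.

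This matches the stated 0.51. Normal quantiles would give 0.426. So the power calculation treated sites as the clusters and allowed for their small number, through t on 6 df. The analysis text states no matching allowance.

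**2. Sites as clusters: analytic check.** With K = 8 equal sites, each containing both arms, the effect estimate is the mean of 8 site-specific differences. The uncorrected sandwich variance is (K − 1)/K times the usual variance of that mean. A z-test at 1.96 therefore rejects when |t₇| > 1.96 × √(7/8) = 1.833, which has probability 10.9%.

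**3. Sites as clusters: simulation.** 10,000 null trials per scenario, about 304-306 participants, baseline-adjusted, two follow-ups averaged. The ranges cover independence and exchangeable working correlation, with and without the stratum in the model.

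| Site sizes | Uncorrected, z | Uncorrected, t on 7 df | Variance × K/(K − 1), t on 7 df |
|---|---|---|---|
| Equal | 10.9-11.2% | 5.9-6.0% | 4.7-4.8% |
| 23-55 | 11.9-12.1% | 6.9-7.3% | 5.6-5.7% |
| 8-80 | 12.8-13.0% | 7.9-8.0% | 6.6-6.7% |

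**4. What causes the excess.** Adding the Rochester/NYC stratum leaves the z-test at 11.0-13.0%, against 10.9-12.9% without it. Adding group effects (ICC 0.0207 to 0.10) gives 11.0-11.2% with equal sites and 13.2-13.4% with very unequal ones. Groups were simulated inside sites, so the site-level sandwich absorbs them. The excess comes from having 8 clusters.

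**5. Participants as clusters.** With no group effect: 4.9-5.3%, or 5.5-5.6% with site fixed effects. With unmodelled groups of 6-10 in the intervention arm:

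| Group ICC (assumed) | False-positive rate |
|---|---|
| 0.0207 | 6.4-7.5% |
| 0.05 | 8.0-10.7% |
| 0.10 | 10.6-15.2% |

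*Hand check.* With one arm clustered, the variance of the difference is inflated by V = 1 + (g − 1)ρ/2. For g = 10 and ρ = 0.05, V = 1.225 and the rate is P(|Z| > 1.96/√1.225) = 7.7%. If baseline adjustment and averaging leave about half the variance (an assumption), the same group variance acts as ρ = 0.10. Then V = 1.45 and the rate is 10.4%, in line with the simulated 10.3-10.7% for groups of 10. The table is thus sensitive to the within-person correlations as well as to group size and ICC.

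**6. Covariates.** No arithmetic applies. Planned analysis describes comparing baseline characteristics by blinded group; Aim 1 then adjusts for whatever the initial analyses identify. The article does not define those analyses or give a selection criterion. Baseline score is the only covariate fixed in advance.

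**The case against.** The strongest reply is that the article never says the site is the GEE cluster. Repeated measures fits participant clusters just as well, and there the rate is about 5% without a group effect. Even with site clusters, 11-13% requires both an uncorrected sandwich and a normal reference. Those details are commonly left to an analysis plan, and a standard correction gives about 5-7%. The power calculation suggests that the few-cluster problem was understood. All of this stands, and it makes the size of the problem conditional.

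A reader might infer something stronger: that the plan's primary test runs at 11-14% because it leaves out the training groups and the stratum, or that it is too optimistic on either reading. The documents do not support this. Omitting the stratum makes no material difference, and omitting the groups makes almost none when sites are the clusters. Unmodelled groups matter only under participant clustering, to a degree set by unstated quantities. The two mechanisms belong to different readings and cannot share one figure.

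The remark about few clusters under Study design is one of three reasons for rejecting other designs; it says nothing about the variance estimator. Fixed effects for all 8 sites go beyond the two-level stratum and are a sound preference rather than the correction of an error.

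On covariates, the defence is that the baseline comparison is blinded, baseline PAM is already fixed and sensitivity analyses are promised. That makes it a modest point of pre-specification. It still stands, because the article states a data-driven rule rather than leaving the matter open.

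**Conclusion.** The concern holds in conditional form. The article describes a robust GEE without naming the cluster, and neither choice is safe as described.

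- **Sites as clusters:** about 11-13% false positives if the sandwich is uncorrected and the reference is normal; about 5-7% with a K/(K − 1) correction and t on 7 df. The cause is the 8 clusters.
- **Participants as clusters:** about 5% with no group effect. With groups of 6-10 the rate is about 6-7.5%, 8-11% and 11-15% at group ICCs of 0.02, 0.05 and 0.10. The article supplies neither group size nor group ICC, so the actual size is unknown.
- **Covariates:** the rule for the primary model is data-driven and does not name the randomisation stratum. This is a separate defect and contributes nothing to the rates above.

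Because this governs the test of the primary outcome, it should be settled before analysis.

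**What to change.** State the primary model in full:

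- **Fixed terms:** treatment, visit, treatment × visit, baseline score and site. The 8 site effects contain the Rochester/NYC stratum.
- **Clustering:** the training group in the intervention arm and the participant in the control arm; or, equivalently in aim, a mixed model with a training-group random effect in the intervention arm only. Use the assigned or scheduled group, so that participants who attend no session stay in the intention-to-treat analysis. Anyone never scheduled forms a cluster of one.
- **Inference:** small-sample degrees of freedom, named in advance.
- **Covariates:** replace the rule on confounders found in initial analyses with this fixed set, and move any others to sensitivity analysis.

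A separate simulation of the clustered version (4,000 null trials per scenario, t on the number of groups minus 1) gave 5.5-6.4%, which is close to nominal but slightly above it. The 10,000-trial runs did not repeat that exact model.

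The cost is analysis wording, a training-group ID for each intervention participant, and somewhat wider intervals than a naive analysis would give. Randomisation and sample size do not change.
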